### **3.3 Recruitment plan**

A pharmacist and/or pharmacy students perform(s) chart reviews for every new patient entering home health and recruitment will come from this allotment of patients. PI will begin screening potential candidates based on these initial chart reviews and using the YouScript® risk analysis tool described in *Section 3.4.1*.

#### **3.3.1 Screening & eligibility assessment**

- Review medical and medication history to determine eligibility based on inclusion/exclusion criteria.
- Obtain and document consent from potential subject on consent form.
- Collect buccal swab for genetic testing (tested group only).

#### **3.3.2 Enrollment/Baseline**

Any new data will be collected during regularly scheduled nursing visits. Principal investigator will review to verify that subjects continue to meet the eligibility criteria.

- Obtain and document consent from subject on study consent form
- Verify inclusion/exclusion criteria
- Obtain demographic information, medical history, medication history, alcohol, and tobacco use history
- Collect blood/urine/saliva/other specimen
- Record results of selected OASIS metrics and PHQ-2
- For those randomized to intervention:
  - Collect buccal swab for testing

### **3.4 Randomization Procedures**

Prior to enrollment the treatment assignments were generated as a simple random sample, with 50 patients in each treatment arm. The randomization was carried out in R version 3.1.1 (Vienna, Austria).

Patients will be numbered chronologically by date of enrollment and each number has been randomized *a priori* to a treatment arm as stated above. Nurses are assigned patients based on coverage area and schedule. Only the PI will have access to the randomization list as to avoid any manipulation of patients to different treatment arms.

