### **4.4 Informed Consent Process**

Extensive discussion of risks and possible benefits of study participation will be provided to subjects and their families, if applicable. A consent form describing in detail the study procedures and risks will be given to the subject. Consent forms will be IRB-approved, and the subject is required to read and review the document or have the document read to him or her. The investigator or designee will explain the research study to the subject and answer any questions that may arise. The subject will sign the informed consent document prior to any study-related assessments or procedures. Subjects will be given the opportunity to discuss the study with their surrogates or think about it prior to agreeing to participate. They may withdraw consent at any time throughout the course of the study. A copy of the signed informed consent document will be given to subjects for their records. The rights and welfare of the subjects will be protected by emphasizing to them that the quality of their clinical care will not be adversely affected if they decline to participate in this study.

The consent process will be documented in the clinical or research record.

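### Section 3.4's safeguard leaves the allocation list with the PI, who also screens and verifies eligibility, so allocation is not concealed from a person who decides on entry

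*Combined protocol and SAP*

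**What the plan says.** Section 3.4 describes one list made in advance: "Prior to enrollment the treatment assignments were generated as a simple random sample, with 50 patients in each treatment arm". Patients are linked to it by order of entry: "Patients will be numbered chronologically by date of enrollment and each number has been randomized" beforehand to an arm. Access is then restricted: "Only the PI will have access to the randomization list as to avoid any manipulation of patients to different treatment arms".

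Two other sections give the PI a part in deciding who enters. Section 3.3: "PI will begin screening potential candidates based on these initial chart reviews and using the YouScript® risk analysis tool". Section 3.3.2: "Principal investigator will review to verify that subjects continue to meet the eligibility criteria".

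Other people are involved too. Under Section 3.3 a pharmacist or pharmacy students do the initial chart reviews. On consent, Section 4.4 says: "The investigator or designee will explain the research study to the subject and answer any questions that may arise".

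Sections 3.3 to 3.6 mention no sealed envelopes, no central or telephone release, no independent holder of the list, and no rule that a patient is irrevocably entered before the arm is seen. Section 2 calls the trial open-label. Section 7 plans Poisson regression for the primary counts and names no baseline covariates. The statistical addendum of March 24, 2016 changes the count model where over-dispersion is found, but adds no adjustment.

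**The concern.** Concealment means that whoever judges whether a patient is suitable, and when to enter that patient, cannot know the arm that comes next. Section 3.4 offers restricted access as the protection against manipulation, but the one person with access also screens and verifies eligibility.

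That person may also hold prognostic information. Section 3.3 has the PI screen with the YouScript risk tool. The form printed under that tool's appendix heading asks about hospitalisation in the last 30 days and about past drug reactions that led to an emergency visit or admission. Both plausibly predict re-hospitalisation and ED use, which are the primary outcomes.

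Numbers follow the date of enrolment, and the text sets no order within a day. Under Section 3.6 a withdrawn subject is replaced by the next number on the same code, so a replacement's arm is equally foreseeable.

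If entry were influenced by the coming arm, even without intent, baseline risk would differ between arms. An analysis without covariates would carry that difference straight into the rate ratio.

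**Working it through.** The plan states no event rate, effect size or power, so there is no figure to reproduce. The check has two parts: tracing roles, and an illustration under assumptions.

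**1. Roles**

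| Step | Who | Where |
|---|---|---|
| Holds the list | PI only | 3.4 |
| Initial chart review | Pharmacist and/or students | 3.3 |
| Screens candidates | PI | 3.3 |
| Discusses consent | Investigator or designee | 4.4 |
| Verifies eligibility at enrolment | PI | 3.3.2 |

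The list holder appears at two steps that decide entry. No step separates that person from the next assignment.

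**2. How predictable is the next arm?** With the list in hand, all 100 assignments can be known. Suppose instead the list were concealed and a recruiter saw only past assignments in this open-label 50:50 list. Best guessing gives m + (4^m / C(2m, m) − 1)/2 correct. With m = 50 this is 50 + (12.56 − 1)/2 = 55.8 of 100. A simulation of 40,000 lists also gave 55.8.

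**3. Rate ratio with no true effect.** Assumed: high-risk patients have 0.8 events per 60 days, low-risk patients 0.3, and half of all patients are high risk. The high-risk share is 0.5 − k in the tested arm and 0.5 + k in controls. The arms move in opposite directions, so the gap is 2k.

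RR = [0.3(0.5 + k) + 0.8(0.5 − k)] / [0.3(0.5 − k) + 0.8(0.5 + k)]

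- k = 0.05 (10-point gap, 2.5 of 50 patients per arm): (0.165 + 0.360)/(0.135 + 0.440) = 0.525/0.575 = 0.913.
- k = 0.10 (20-point gap, 5 of 50 per arm): (0.18 + 0.32)/(0.12 + 0.48) = 0.50/0.60 = 0.833.

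**4. False-positive rate.** Two-sided 0.05 Wald test on the log rate ratio, 50 per arm, Poisson variance. Let z = |ln RR| / √(1/events₁ + 1/events₂). The rate is Φ(z − 1.96) + Φ(−z − 1.96).

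- 10-point gap: 26.25 and 28.75 expected events, SE 0.270, z = 0.091/0.270 = 0.34, rate about 6%.
- 20-point gap: 25 and 30 expected events, SE 0.271, z = 0.182/0.271 = 0.67, rate about 10%.

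**5. Range.** Now let the geometric-mean count μ run from 0.3 to 0.8 per patient, with arm means μ√RR and μ/√RR. The same formula gives:

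| Rate ratio from selection alone | False-positive rate |
|---|---|
| 0.9 | 6–8% |
| 0.8 | 9–17% |
| 0.7 | 16–35% |

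**The case against.** **Nobody is said to enrol alone, and nothing shows the list was used.** This stands. Chart review and consent involve others, and the text shows that the next arm is knowable, not that it was looked up before each entry. The rule also does real work by keeping the list from nurses and other staff. A reader might infer that the PI controlled enrolment, or that patients were steered. The documents support neither.

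**The swab.** Section 3.3.1 lists the tested-group swab under screening. A reader might infer that the arm was acted on before eligibility was final. Section 3.3.2 lists the swab for those already randomised to intervention, after consent, eligibility and baseline measures, and Appendix A puts testing at Day 0. This is a duplicated entry to reconcile, not evidence of early unmasking.

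**PI outcome entry.** The PI also enters the outcomes (5.1). That concerns ascertainment rather than allocation. Home health staff record re-hospitalisations and nurses report ED visits before the PI transcribes them.

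**The illustrated sizes are modest.** This stands. With half the patients high risk, the chance gap between two arms of 50 has SD √(2 × 0.25/50) = 10 points. The two cases are thus 1 and 2 SD of what chance gives under perfect concealment. But chance gaps fall in either direction and are what the 5% error rate is meant to allow for, whereas steering need not be balanced. For the same reason, a baseline table without a striking imbalance cannot rule steering out.

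**It is a finished pilot.** That limits the remedy. It does not remove the point, since Section 1.3 states a directional hypothesis and Section 7 tests at P < 0.05.

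**Conclusion.** The concern holds in this form: the safeguard in Section 3.4 does not cover a person who screens and verifies eligibility, so allocation was not concealed from the PI under the protocol as written. This rests on the documents' own text and needs no assumption.

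The size does rest on assumptions: event rates of 0.8 and 0.3, an even risk mix, opposite shifts in the two arms, and Poisson variance. Under these, gaps of 10 and 20 points produce null rate ratios of 0.91 and 0.83 and false-positive rates of about 6% and 10%. Other assumed rates and stronger selection give the wider range shown in the working. The documents establish opportunity for selection bias; whether any occurred, and how much, cannot be determined from them.

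**What to change.** **Protocol text, or a successor trial.** Replace the access sentence in Section 3.4 with wording such as: *The list is held by a person who does not screen, enrol or enter outcomes, or is kept in sequentially numbered opaque sealed envelopes. The arm is released only after consent, eligibility and baseline OASIS and PHQ-2 are recorded and the patient number is logged with date and time.* Reconcile the swab entry in 3.3.1 with 3.3.2 and Appendix A. The cost is a few lines of text and one call or envelope per patient.

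**This trial.** The addendum of March 24, 2016 postdates study completion, so only reporting and analysis can change:

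- State that allocation was not concealed from the PI.
- Report the baseline comparison by arm.
- Add, as a sensitivity analysis, the four primary rate ratios (re-hospitalisations and ED visits at 30 and 60 days) adjusted for age and admission M1034. Use the count model chosen for the unadjusted comparison. State how the UK category of M1034 is handled, for example as its own level.
- Say that adjustment cannot remove selection on unmeasured risk.

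Age and admission M1034 are already on the data entry form (Appendix C), so this needs no new data: one baseline table, four extra models and a sentence in the limitations.

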### 3.4.1 YouScript® Personalized Prescribing System

The risk for a drug-drug, drug-gene, or drug-drug-gene interaction will be determined at baseline for each tested patient by conducting a risk analysis using the YouScript® risk analysis tool. The risk analysis tool uses an algorithm based on the baseline list of medications being taken by the patient in combination with the U.S. gene frequencies for CYP2D6, CYP2C9, CYP2C19, CYP3A4, CYP3A5 to produce the number of known drug-drug interactions, potential additional drug-gene and drug-drug-gene interactions, and the percentage likelihood that at least one more major interaction will be revealed with testing. In addition to matching on other variables, the risk analysis tool will be used on the untested group as well.

At the time of this writing, the standard panel of tests included in the YouScript® Personalized Prescribing System includes PCR based assays to detect the following alleles, including all common and most rare variants with known clinical significance at analytical sensitivity and specificity >99%:

- CYP2C19: active \*1; inactive \*2, \*3, \*4, \*5, \*6, \*7, \*8, \*12; partially active \*9, \*10; rapid \*17
- CYP2D6: active \*1, \*2; \*2A, \*35; inactive \*3, \*4, \*5, \*6, \*7, \*8, \*10, \*11, \*12, \*14, \*15, \*19, \*20, \*36; partially active \*9, \*17, \*29, \*41; gene duplications \*1, \*2, \*4, \*10, \*41
- CYP2C9: active \*1; inactive \*2, \*3, \*4, \*5, \*6, \*8, \*11, \*13, \*15
- VKORC1: high sensitivity 1639G>A
- CYP3A4: active \*1; partially active \*22
- CYP3A5: active \*1; inactive \*3

The report provided to the clinician includes the tests conducted, the patient's phenotype for each gene tested (poor metabolizer, intermediate metabolizer, normal metabolizer, rapid metabolizer, ultra rapid metabolizer), the genotype for each gene tested, type and time of sample collection, the medications the patient is taking, the prescribing suggestions (including change, consider, monitor), the type of interaction (e.g., drug/gene, drug/drug/gene, drug/drug), interpretation of the results, and the clinical indication for testing.

The genetic test will be performed by Genelex whereas all other procedures are performed in accordance with usual care practice.

### 3.4.2 Drug Information Resources (for controls)

Standard drug information resources will be used (e.g., Lexicomp Online) in accordance with usual care practice. These systems contain such knowledge as drug-drug and drug-disease interactions, minimum and maximum dosing suggestions, drug-allergy cross-sensitivity groupings, and groupings of medications by therapeutic class.

---

### **3.5 Retention Plan**

Subjects who are enrolled in the study and are discharged from home health prior to the initial 60 days will be contacted via telephone to encourage retention.

### **3.6 Subject Withdrawal**

Subjects are free to withdraw from participation in the study at any time upon request.

An investigator may terminate a study subject's participation in the study if:

- Any clinical adverse event (AE), laboratory abnormality, or other medical condition or situation occurs such that continued participation in the study would not be in the best interest of the subject.
- The subject meets an exclusion criterion (either newly developed or not previously recognized) that precludes further study participation.

If subjects are still under care of home health then the investigator will continue to make drug therapy recommendations per usual standard of care.

New patients will be enrolled to replace withdrawn subjects, continuing chronological enrollment numbering, and will be randomized according to the randomization code.

This study may be suspended or prematurely terminated if there is sufficient reasonable cause. Written notification, documenting the reason for study suspension or termination, will be provided by the suspending or terminating party to investigator and regulatory authorities.

If the study is prematurely terminated or suspended, the principal investigator will promptly inform the IRB and will provide the reason(s) for the termination or suspension.

Circumstances that may warrant termination include, but are not limited to:

- Determination of unexpected, significant, or unacceptable risk to subjects.
- Insufficient adherence to protocol requirements.
- Data that is not sufficiently complete and/or evaluable.
- Determination of futility.

## **4 ETHICAL CONSIDERATIONS**

### **4.1 Statement of compliance**

The study will be conducted in accordance with the International Conference on Harmonisation guidelines for Good Clinical Practice (ICH E6), the Code of Federal Regulations on the Protection of Human Subjects (45 CFR Part 46). All personnel involved in the conduct of this study have completed human subjects protection training.

### **4.2 Risks**

Genetic testing poses no risk to the patient.

### **4.3 Benefits**

Potential benefits include therapeutic treatment levels, decreased adverse effects, decreased hospitalizations and emergency department visits, decreased pill burden, decreased cost to patients and healthcare systems, and improvement in quality of life.

### **4.4 Informed Consent Process**

Extensive discussion of risks and possible benefits of study participation will be provided to subjects and their families, if applicable. A consent form describing in detail the study procedures and risks will be given to the subject. Consent forms will be IRB-approved, and the subject is required to read and review the document or have the document read to him or her. The investigator or designee will explain the research study to the subject and answer any questions that may arise. The subject will sign the informed consent document prior to any study-related assessments or procedures. Subjects will be given the opportunity to discuss the study with their surrogates or think about it prior to agreeing to participate. They may withdraw consent at any time throughout the course of the study. A copy of the signed informed consent document will be given to subjects for their records. The rights and welfare of the subjects will be protected by emphasizing to them that the quality of their clinical care will not be adversely affected if they decline to participate in this study.

The consent process will be documented in the clinical or research record.

### **4.5 Subject Confidentiality**

Subject confidentiality is strictly held in trust by the investigator, study staff, and the sponsor and their agents. This confidentiality is extended to cover testing of biological samples and genetic tests in addition to any study information relating to subjects.

The study protocol, documentation, data, and all other information generated will be held in strict confidence. No information concerning the study or the data will be released to any unauthorized third party without prior written approval of the sponsor.

The study monitor or other authorized representatives of the sponsor may inspect all study documents and records required to be maintained by the investigator, including but not limited to, medical records (office, clinic, or hospital) for the study subjects. The clinical study site will permit access to such records.

### **4.6 Institutional Review Board**

The protocol, informed consent form(s), recruitment materials, and all subject materials will be submitted to the Harding University IRB for review and approval. Approval of both the protocol and the consent form must be obtained before any subject is enrolled. Any amendment to the protocol will require review and approval by the IRB before the changes are implemented in the study.

### **4.7 Reporting Unanticipated Problems to the IRB**

The Office for Human Research Protections (OHRP) considers unanticipated problems involving risks to subjects or others to include, in general, any incident, experience, or outcome that meets **all** of the following criteria:

- unexpected in terms of nature, severity, or frequency given (a) the research procedures that are described in the protocol-related documents, such as the IRB-approved research protocol and informed consent document; and (b) the characteristics of the subject population being studied;
- related or possibly related to participation in the research (“possibly related” means there is a reasonable possibility that the incident, experience, or outcome may have been caused by the procedures involved in the research); and
- suggests that the research places subjects or others at a greater risk of harm (including physical, psychological, economic, or social harm) than was previously known or recognized.

#### **4.8 Unanticipated Problem Reporting to IRB**

Incidents or events that meet the OHRP criteria for unanticipated problems require the creation and completion of an unanticipated problem report form. OHRP recommends that investigators include the following information when reporting an adverse event, or any other incident, experience, or outcome as an unanticipated problem to the IRB:

- Appropriate identifying information for the research protocol, such as the title, investigator’s name, and the IRB project number;
- A detailed description of the adverse event, incident, experience, or outcome;
- An explanation of the basis for determining that the adverse event, incident, experience, or outcome represents an unanticipated problem;
- A description of any changes to the protocol or other corrective actions that have been taken or are proposed in response to the unanticipated problem.

To satisfy the requirement for prompt reporting, unanticipated problems will be reported using the following timeline:

- Unanticipated problems that are serious adverse events will be reported to the IRB within 1 week of the investigator becoming aware of the event.
- Any other unanticipated problem will be reported to the IRB within 2 weeks of the investigator becoming aware of the problem.
- All unanticipated problems should be reported to appropriate institutional officials (as required by an institution’s written reporting procedures), the supporting agency head (or designee), and OHRP within one month of the IRB’s receipt of the report of the problem from the investigator.

## **5 DATA MANAGEMENT CONSIDERATIONS**

### **5.1 Outcome measures**

The following outcome measures will be recorded by the nurse upon patient admission, Day 30, and Day 60. PI will extract the data from patient charts and manually enter the data into the data entry form (Appendix C):

| Endpoint              | Indicator   | Scale                                                                                                                                                                                                                                                                                                                                                                                                                                                                                                                                                                                                                                                         |
|-----------------------|-------------|---------------------------------------------------------------------------------------------------------------------------------------------------------------------------------------------------------------------------------------------------------------------------------------------------------------------------------------------------------------------------------------------------------------------------------------------------------------------------------------------------------------------------------------------------------------------------------------------------------------------------------------------------------------|
| Overall status        | OASIS M1034 | 
0 - The patient is stable with no heightened risk(s) for serious complications and death (beyond those typical of the patient's age).
 
1 - The patient is temporarily facing high health risk(s), but is likely to return to being stable without heightened risk(s) for serious complications and death (beyond those typical of the patient's age).
 
2 - The patient is likely to remain in fragile health and have ongoing high risk(s) of serious complications and death
 
3 - The patient has serious progressive conditions that could lead to death within a year.
 
UK - The patient's situation is unknown or unclear.
 |
| Pain                  | OASIS M1242 | 
0 - Patient has no pain
 
1 - Patient has pain that does not interfere with activity or movement
 
2 - Less often than daily
 
3 - Daily, but not constantly
 
4 - All of the time
                                                                                                                                                                                                                                                                                                                                                                                                                                                 |
| Confusion             | OASIS M1710 | 
0 - Never
 
1 - In new or complex situations only
 
2 - On awakening or at night only
 
3 - During the day and evening, but not constantly
 
4 - Constantly
 
NA - Patient nonresponsive
                                                                                                                                                                                                                                                                                                                                                                                                                                      |
| Anxiety               | OASIS M1720 | 
0 - None of the time
 
1 - Less often than daily
 
2 - Daily, but not constantly
 
3 - All of the time
 
NA - Patient nonresponsive
                                                                                                                                                                                                                                                                                                                                                                                                                                                                                                |
| Depression            | PHQ-2[1]    | 
0 – Not At all
 
1 – Several Days
 
2 – More Than Half of the Days
 
3 – Nearly Every Day
                                                                                                                                                                                                                                                                                                                                                                                                                                                                                                                                               |
| Disruptive behavior   | OASIS M1745 | 
0 - Never
 
1 - Less than once a month
 
2 - Once a month
 
3 - Several times each month
 
4 - Several times a week
 
5 - At least daily
                                                                                                                                                                                                                                                                                                                                                                                                                                                                                      |
| ADL & IADL assistance | OASIS 2110  | 
1 - At least daily
 
2 - Three or more times per week
 
3 - One to two times per week
 
4 - Received, but less often than weekly
                                                                                                                                                                                                                                                                                                                                                                                                                                                                                                        |

| Endpoint | Indicator | Scale                                                               |
|----------|-----------|---------------------------------------------------------------------|
|          |           | 5 - No assistance received
UK - Unknown [Omit "UK" option on DC] |

Re-hospitalizations and dates of admission are manually recorded, by a member of the home health staff, on a white board displayed in the home health office. PI will manually enter the re-hospitalizations and time to first re-hospitalization on the data entry form for each patient.

Nurses will report ED visits, falls, and adverse drug reactions to PI as well as document in patient chart. PI will manually enter the information into the data entry form.

Additionally, for those patients who received the intervention, the study pharmacist and prescribers will be asked about impact of YouScript® testing on clinical decision-making.

